## Abstract

**Background:**

Diabetes is one of the four main types of noncommunicable or chronic diseases. Iran is among the countries with the highest incidence of diabetic patients. A study demonstrated that the collection of diabetic data is neither organized nor standardized. There is currently no instance of electronic personal health records particularly used for diabetic patients in Iran, hence the need for one, which will be useful for self-care of diabetic patients.

**Objective:**

The objective of the study is to examine the impact of a Web-based diabetic personal health record (DPHR) on the self-care status of diabetic patients as compared with the control group.

**Methods:**

This study is a randomized control trial, which involves a systematic review of literature of the preferred data elements regarding a DPHR, and reevaluating the results with the opinions of local endocrinologists. Inclusion criteria were as follows: type 2 diabetic patients between 20-70 of age who live in the Mashhad City and having the disease for at least one year. The sample size is 72 people that were randomly assigned to the control and intervention groups. The participants in the intervention group were allowed access to the Web-based DPHR system, while those in the control group will continue to receive the usual care for 4 months. The study primary outcome measures include self-care status of participants and planned visit adherence.

**Results:**

At the moment, there is an ongoing recruitment of participants, and preliminary results will be published in early 2016.

**Conclusions:**

We expect the final DPHR model, developed and tested during this study, to help diabetic patients to actively participate in their care management process, and also to empower the physician in providing more quality informed decisions regarding their patients.

**Trial Registration:**

irct.ir IRCT2013082914522N1; http://www.irct.ir/searchresult.php?id=14522&number=1 (Archived by WebCite at http://www.webcitation.org/6cC4PCcau).

## Introduction

### Diabetes Definition

Diabetes is one of the four main types of chronic or noncommunicable diseases [1], and its management is of great concern to the society and world at large [2-5]. A definition by the World Health Organization [6] states that: “Diabetes is a chronic disease that occurs either from insufficient production of insulin by the pancreas or ineffective use of produced insulin”. Type 2 diabetes results from the body’s ineffective use of insulin.

Lack of or insufficient care for a diabetic patient can result in several complications such as diabetic neuropathy, retinopathy, nephropathy, diabetic foot, and myocardial infarction [2]. However, continuous blood glucose and blood pressure monitoring, timely visits, appropriate physical activity, blood lipids control, and periodical examinations, as foundation of diabetes self-management, can help patients lessen these complications [7-9].

In recent times, there has been increasing prevalence of diabetes globally, with the low- and middle-income countries having the highest prevalence. The global prevalence of diabetes was estimated to be 9% in 2014 [10], with an estimated increase of 366,000,000 worldwide and 6,421,000 in Iran by 2030 [11,12]. In order to manage the increasing number of diabetics in the future [13,14], and to reduce the workload of health care providers, there is a need to redefine the role of diabetes management centers [15]. Patients who have more knowledge about their disease and procedures are more proficient at communicating experiences and then become a useful asset in long-term care [16]. In this way, Web-based personal health records (PHRs) provide patients with access to their health information [17-19].

### Personal Health Records

Application of PHRs, in general, and diabetes-specific PHRs, has been growing very rapidly. Studies have demonstrated that Web-based diabetes management tools can improve self-care activities [19] and biomedical outcomes measures such as glycated hemoglobin (HbA1c), low-density lipoprotein (LDL) cholesterol, blood pressure, and body mass index (BMI) [20-24]. The benefits of PHRs in supporting self-management is clear, especially in facilitating communications among health care providers and supporting information access [25].

Iran is among the countries with the highest incidence of diabetic patients [26]. A recent study demonstrated that the collection of diabetic data are neither organized nor standardized [27]. There are no diabetic PHRs (DPHRs) used to organize diabetes data in the country.

This multiphase study involves: (1) a systematic review of literature regarding the preferred data elements regarding a DPHR, (2) an afterward refinement of data elements by the local endocrinologists, (3) a systemic development of a Web-based DPHR application (app), and (4) final evaluation of the model through a randomized controlled trial. The researchers hope that the final model developed throughout in this study will help diabetes patients to actively participate in their treatment plan, and also optimize the decision making process of the diabetes physicians in their everyday practice.

### Study Hypothesis

The participants assigned to receive the DPHR tool will manage better self-care as compared to those who receive only usual care.

## Methods

### Randomization and Blinding

After the provision of informed consent, participants are randomly allocated to the control or intervention arm stratified by gender (male, female), employment status (employed and nonemployed), and age groups (=<30; 30-50; and =>50 years of age), that is, the covariate adaptive random allocation is considered. The random allocation sequence will be done through a concealed and computerized random number program [28]. A person who has no direct involvement in this trial will do the randomization process. Also, we note that the participants and attending physician (RA) can’t be blinded to the use of PHRs because the artefact is obvious, but the chief researcher (MT) and data analyst ([name]) are blinded to the participants during the trial. To minimize contamination of the trial, the subjects in the intervention arm will be required not to interact and share their DPHRs information with other participants in the control arm.

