### Study Design

A four-phase approach, including a systematic review of evidence regarding DPHR development, usability testing, iterative refinement, and intervention evaluation will be utilized. A randomized controlled trial (RCT) with a 2-arm parallel design and allocation ratio of 1:1 will be used to evaluate the impact of DPHRs on self-care. Repeated assessments will be conducted at two time points, including baseline and postintervention, over a 4-month trial period. The patients in the intervention group will be allowed access to the Web-based app, while those in the control group will be receiving usual care throughout the study period.

The DPHR interface will be designed in three types, covering our three groups of users including the participating patients, the clinic staff, and the physicians. The chief researcher will be the system administrator. Reminders via a short message service (SMS), telephone contact, and email will be used for visiting the website.

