### Ethical Considerations

The Research Review Committee as well as the Regional Ethics Committee (approval # 921835) approved the trial. The trial is registered on the Iran Registry of Clinical Trials [30].

The informed written consent will be obtained from the eligible participants, with its content clearly explained to the subjects by the trial assistant. During the project, participants will be given means of communication in order to share their questions and concerns.

The research tools, including questionnaires, will be completely anonymous. However, a unique code will be included in each form in order to manage further references. Access to the DPHR Internet app requires a user name and password, which are provided by the trial assistant. All participants’ information will be securely stored and will only be accessible to authenticated trial team members.

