### Intervention Development

The Web-based DPHR app is designed to empower diabetes patients with self-care information and tools. The major aim of this study is to systematically develop an evidence-based Internet app, which is ultimately validated by the local endocrinologists. The app allows participants to easily enter their monitoring data, to view their history of progress, to get informed about their appointment schedule, and to learn about their disease. The patients will also be able to share the blood glucose and lab result trends with their physicians for further advices.

The participants in the intervention arm will receive the Web-based app as well as usual care. On the other hand, the control arm will continue to receive usual care.

The trial team and the software provider will be in charge of the DPHR development, updates, and maintenance. The app interface will be evolved and optimized throughout the trial using heuristic usability evaluation techniques [31] by medical informatics specialists, endocrinologists, and also the participants.

The trial will last for 4 months. The major treatment process delivered by the attending physicians will not have any impact on the intervention and vice versa. During the study, participants may receive extra visits and lab tests in addition to their routine care plan, in order to keep careful track of changes in their health information.

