### Analysis Plan

All analyses will be 2-tailed and statistical significance is considered as a *P* value of ≤.05. Data will be analyzed using SPSS. χ^2^ test will be used for determining differences in subject groups based on data collected from baseline, and postintervention (significance interval of 95% will be considered). A *t* test will be used to compare the control and intervention groups, while a chi-square test will be used for continuous and categorical variables, respectively. The distribution of variables, website usage statistics, and website user satisfaction are examined using descriptive analysis.

Examination of the impact of the DPHR tool on self-care will be performed using a linear mixed model at the end of the trial period. The longitudinal nature of data collection will result in a repeat in the measure of analysis of variance using data from all trial assessment points. Missing values will be handled using multiple imputation [35]. All analyses will be done according to intention-to-treat principle.

Before inferential analysis, the homogeneity of variances of distributions in the study groups will be confirmed. The sequential logistic regression will be used for adjusting baseline characteristics and possible confounders. Dropouts from the study will be measured by no-use of the app tool for more than one month. Also, participants in the intervention group must enter blood glucose measurements at home (FBS, bedtime, 2 hours after lunch, and 2 hours after dinner) at least four times a week, otherwise, they are eliminated from the trial. The access data will be assessed using the Web server access log.

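### The chief researcher is declared blinded but also administers the DPHR system, in which only intervention-arm patients hold patient accounts

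*Protocol article*

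**What the plan says.** Under Randomization and Blinding, the protocol article accepts that participants and the attending physician know who uses the health record. It then states that the chief researcher and the data analyst "are blinded to the participants during the trial".

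Other sections bear on that statement:

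- **Study Design** describes an interface for "three groups of users including the participating patients, the clinic staff, and the physicians" and adds: "The chief researcher will be the system administrator".
- **Study Design** also says "The patients in the intervention group will be allowed access to the Web-based app", and **Intervention Development** says "the control arm will continue to receive usual care".
- **Ethical Considerations** says: "Access to the DPHR Internet app requires a user name and password, which are provided by the trial assistant". Participants' information "will only be accessible to authenticated trial team members". Research forms are anonymous but carry a unique code.
- **Analysis Plan** defines dropout by more than one month without app use. It removes intervention participants who enter home glucose values on fewer than four occasions a week. On usage it says: "The access data will be assessed using the Web server access log".
- **Trial Population and Recruitment Procedure** allows exclusion after inclusion when a participant cannot keep cooperating, with an open-ended list of reasons.
- **Data Collection** assigns the questionnaire interviews to someone outside the trial team.

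**The concern.** One person is given two roles that do not fit together. Blinding to allocation means not knowing who has the app, while administering the app normally means being able to see who has an account.

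This matters because the trial is otherwise open. Participants and physician know the allocation, and the self-care outcome is reported by those participants. The plan also contains decisions after randomization that leave room for judgement, or that depend on data held in the system: exclusion for inability to cooperate, dropout for non-use, and elimination for too few glucose entries. A reader told that the trial lead is blinded will take it that the lead could not steer such decisions by arm. If the lead can see the accounts, that reassurance is unfounded.

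**Working it through.** The article gives no figure to reproduce and the point needs no calculation beyond a count. The check sets the statements side by side.

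1. **What the blinding claim covers.** Randomization and Blinding contrasts people who cannot be blinded to use of the record with two people who are blinded. In that contrast the claim concerns allocation, not only names. It covers the chief researcher and the data analyst.

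2. **Who administers the system.** Study Design names the chief researcher.

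3. **Which patients are in the system.** Intervention-arm patients get access and controls stay on usual care. Clinic staff and physicians are users too, so the whole user list is not the allocation list. The patient part of it corresponds to the intervention arm. The article does not say this in so many words; it follows from who is given access.

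4. **What an administrator could learn.** Sample Size plans 36 participants per arm. If patient accounts are visible to the administrator, the 36 intervention participants can be recognised by having one. The controls follow by elimination (72 − 36 = 36) only if the administrator also holds an enrolment list that can be linked to the accounts. The article does not say whether that is so.

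5. **Is there a safeguard?** None is described. The trial assistant hands out the credentials, but nothing says the administrator cannot see the resulting accounts. Codes on the research forms could hide names. If the accounts used the same codes, they would still show which codes belong to the intervention arm. The access rule under Ethical Considerations admits authenticated trial team members and makes no exception for anyone declared blinded.

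6. **Does the same conflict reach the data analyst?** No section gives the analyst a role in the system. The Analysis Plan does not say who reads the access log, or whether this happens before or after the main analysis. The analyst's blinding is therefore not contradicted.

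7. **Where could knowledge of allocation act?** Hardly on outcome collection, since the interviewer is outside the trial team. It could act on exclusion, elimination and data handling, if the chief researcher has any part in them. The article does not say who makes those decisions.

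**The case against.** The strongest reply is that this is an inconsistency between two sentences, with little shown to follow from it. The plan has other protections: a concealed computerized sequence, randomization by someone not directly involved in the trial, an external interviewer, and intention-to-treat analysis with multiple imputation. The scope of the administrator role is not described and could be purely technical. The outcome is self-reported by unblinded participants, so the chief researcher's blinding has little direct effect on it. The glucose-entry rule is written for one arm, so whoever applies it knows the arm in any case.

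Much of this stands, and it limits the point. A reader might infer four stronger things that the article does not support:

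- **That all the stated blinding fails.** Nothing contradicts the analyst's blinding. It would be at risk only if usage data reached the analyst before the main analysis, which the article does not say.
- **That the chief researcher makes exclusion, cleaning or modelling decisions knowing the arms.** No section assigns these decisions to anyone.
- **That allocation is revealed for all 72 participants.** This needs a linked enrolment list, which is not described.
- **That the administrator sees individual glucose entries.** This too depends on the undescribed scope of the role.

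The objection does not remove the conflict for the chief researcher. Nor does it help that an article condenses a fuller protocol: the difficulty is not a missing detail but two printed statements that do not fit together.

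**Conclusion.** The point holds for the chief researcher only. The article declares this person blinded and also makes them administrator of a system whose patient accounts identify the intervention arm, with no safeguard described. The design as printed does not support the claim.

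This rests on two assumptions: that an administrator can see patient accounts, and that no control participant has one. The first is the ordinary meaning of the role; the second follows from the description of the arms.

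In size, up to 36 allocations are recognisable directly, and the other 36 only with a linked enrolment list. The resulting bias, if any, cannot be computed. It would come through influence on post-randomization exclusion, elimination and data handling rather than through outcome collection. The matter should be corrected, but it does not by itself undermine the trial.

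**What to change.** Reconcile Randomization and Blinding with Study Design:

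- **Move the role.** Give system administration to a team member not declared blinded. The trial assistant is a natural choice, since that person already issues the credentials. Withhold account-level access from the chief researcher until the primary analysis is locked, and state who holds the account list. Handing the role to the software provider is less suitable: Intervention Development names the provider separately from the trial team, and Ethical Considerations limits participant information to authenticated team members.
- **Protect the analyst's blinding at little cost.** Release the self-care data with the arms coded and without app-use variables, which would give the code away.
- **Otherwise correct the claim.** If the chief researcher has already had administrator access, or the role is not moved, withdraw the statement that this person is blinded. The article reports recruitment as under way, and moving the role cannot restore blinding already lost.

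The cost is one reassigned access role and a coded data release, or the deletion of one clause. Sample size, outcomes and analysis model are unaffected. No option blinds whoever applies the one-arm glucose-entry rule, so the plan should not suggest that it does.

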### Study Design

A four-phase approach, including a systematic review of evidence regarding DPHR development, usability testing, iterative refinement, and intervention evaluation will be utilized. A randomized controlled trial (RCT) with a 2-arm parallel design and allocation ratio of 1:1 will be used to evaluate the impact of DPHRs on self-care. Repeated assessments will be conducted at two time points, including baseline and postintervention, over a 4-month trial period. The patients in the intervention group will be allowed access to the Web-based app, while those in the control group will be receiving usual care throughout the study period.

The DPHR interface will be designed in three types, covering our three groups of users including the participating patients, the clinic staff, and the physicians. The chief researcher will be the system administrator. Reminders via a short message service (SMS), telephone contact, and email will be used for visiting the website.

### Trial Population and Recruitment Procedure

The inclusion criteria for participants are as follows: the patient must be a male or female with type 2 diabetes, age between 20 and 70 years, with a minimum diabetes history of one year (according to the primary diagnosis date), must live in the city of Mashhad, must be fairly computer literate, and have access to the Internet. The included participants must be able to provide informed consent.

We excluded the already included participants, if they, for any reason, decided to terminate the participation, or were unable to actively continue the required cooperation, due to sickness, pregnancy, and etc.

The trial will be conducted in Mashhad City (Iran), with participants being recruited from one endocrinology practice unit. The number of diabetic patients is estimated to be above 120,000 in Mashhad [29]. We will start the study with the acquisition of baseline information including age, education level, gender, self-care score, HbA1c, weight, employment status, length of disease, and diagnosis date along with the information required to check the inclusion eligibility. Only the qualified participants will be given the consent form.

After signing the consent form, participants will be randomized into either the intervention or the control arm. After providing confirmed consent, a package including a copy of the consent form, welcome letter, and a take-home manual, along with step-by-step directions for using the website will be rendered manually to the participants. The participants are allowed to communicate with the trial team through email or telephone, sharing their questions and concerns. For assuring the quality of trial, the trial assistant will be trained during several sessions regarding the interaction with the website, the potential questions and answers of the participants, and the intervention process.

### Ethical Considerations

The Research Review Committee as well as the Regional Ethics Committee (approval # 921835) approved the trial. The trial is registered on the Iran Registry of Clinical Trials [30].

The informed written consent will be obtained from the eligible participants, with its content clearly explained to the subjects by the trial assistant. During the project, participants will be given means of communication in order to share their questions and concerns.

The research tools, including questionnaires, will be completely anonymous. However, a unique code will be included in each form in order to manage further references. Access to the DPHR Internet app requires a user name and password, which are provided by the trial assistant. All participants’ information will be securely stored and will only be accessible to authenticated trial team members.

### Intervention Development

The Web-based DPHR app is designed to empower diabetes patients with self-care information and tools. The major aim of this study is to systematically develop an evidence-based Internet app, which is ultimately validated by the local endocrinologists. The app allows participants to easily enter their monitoring data, to view their history of progress, to get informed about their appointment schedule, and to learn about their disease. The patients will also be able to share the blood glucose and lab result trends with their physicians for further advices.

The participants in the intervention arm will receive the Web-based app as well as usual care. On the other hand, the control arm will continue to receive usual care.

The trial team and the software provider will be in charge of the DPHR development, updates, and maintenance. The app interface will be evolved and optimized throughout the trial using heuristic usability evaluation techniques [31] by medical informatics specialists, endocrinologists, and also the participants.

The trial will last for 4 months. The major treatment process delivered by the attending physicians will not have any impact on the intervention and vice versa. During the study, participants may receive extra visits and lab tests in addition to their routine care plan, in order to keep careful track of changes in their health information.

